##### Control arm

Adults: streptomycin 1 g twice daily for 5 days with ciprofloxacin 500 mg orally twice daily (or ciprofloxacin 400 mg twice daily IV for those who cannot take it orally) for 10 days.Children: streptomycin 15 mg/kg twice daily for 5 days with ciprofloxacin 15 mg/kg twice daily (max 500 mg per dose) orally (or 10 mg/kg IV twice daily for those who cannot take it orally—maximum dose 400 mg) for 10 days. This is the alternative treatment proposed by the Ministry of Public Health since the 2018–2019 plague season.Patients who start taking intravenous ciprofloxacin may switch to oral administration once they are able to swallow or once deemed clinically appropriate by the treating physician.

#### Route of administration

Streptomycin is administered intramuscularly to all patients in the control group. Ciprofloxacin is administered orally, except for patients with the following manifestations:
VomitingUnable to swallowUnconsciousSystolic blood pressure < 90 mmHgAny other conditions or situations for which the physician decides that intravenous treatment is indicated

#### Timing of dosing

Ciprofloxacin: doses will be administered morning and evening.Streptomycin: doses will be administered morning and evening.

#### Duration of therapy

The study drugs will be administered for a total of 10 days. After 10 days, the decision whether to continue therapy will be at the treating physician’s discretion.

#### Dosing duration justification

We are using 10 days of therapy in both the ciprofloxacin arm and streptomycin and ciprofloxacin arm as this is the current standard duration of plague treatment in Madagascar. To date, the only RCT in plague used 7 days of therapy (gentamicin versus doxycycline) in both groups.

#### Prohibited drugs

TheophyllineWarfarin

### Criteria for discontinuing or modifying allocated interventions {11b}

If, for any reason, a dose of the study drug is not administered at the scheduled time, it may be administered later, but not more than 6 h after the scheduled time of administration. No dose adjustment is planned.

### Strategies to improve adherence to interventions {11c}

The trial will be co-managed by IPM who will deploy a clinical research associate and two clinical study nurse to each district to assist with the recruitment, trial procedures and data entry. These members of staff will be based in the districts for the duration of each season.

Before activation, site investigators will receive training on the identification of plague patients and the study protocol. After activation, the site investigators will be responsible for patient management alongside the clinical study nurse.

To optimize patient compliance, community health workers (CHWs) in each district will be trained to identify cases of plague based on community case definition as per the national guideline, refer patients to the local CSB I/II, perform treatment visits to patient homes and complete the treatment record for each home-based visit. At the time of discharge from the facility, patients will also be equipped with a mobile phone, as follow-up visits on D11 and D21, and possibly M3 will require a return visit to the treating CSB.

At the beginning of each new plague season, all site staff will be retrained on the trial protocol and reinitiated to the trial. This will reinforce the protocol following the annual recruitment suspension and ensure that, due to high staff turnover at the CSBs, any new staff members receive the same comprehensive training as those who were trained at the original initiation visit.

A monitoring plan has been developed to ensure regular reviews of trial data and site compliance with the protocol. These reviews will be completed within 72 h of each of the first five patients being recruited at each site, annually at the end of each plague season and on the identification of persistent or serious protocol violations and serious breaches. The Trial Operations Committee (TOC) will also meet on a weekly basis to review recruitment and compliance and discuss any other issues affecting the trial.

The trial has also appointed a Data Safety Monitoring Board (DSMB) and Trial Steering Committee, who will meet regularly to discuss the management of the trial.

### Relevant concomitant care permitted or prohibited during the trial {11d}

Other treatments, including the administration of fluids and organ support, will be at the discretion of the treating clinician.

### Provisions for post-trial care {30}

#### Post-trial care

Following their exit from the trial, patients will return to their standard care pathway.

#### Insurance

The University of Oxford, as study sponsor, has arranged appropriate insurances to provide for the University’s responsibilities to research subjects and to cover the legal liabilities of the University to those engaged by the University in the performance of this research.

### Outcomes {12}

#### Primary endpoint

The proportion of patients with bubonic plague with a therapeutic response (assessed on D11). Therapeutic response is defined as follows for subjects with a visible and measurable bubo:
AliveResolution of fever (uncorrected axillary temperature < 37.5 °C)A ≥ 25% decrease in bubo size (in the case of multiple buboes, the largest bubo)Has not received alternative treatment for plagueNo clinical decision to continue anti-plague antibiotics beyond day 10

For patients with small buboes that are palpable but not measurable:
AliveAbsence of fever (uncorrected axillary temperature < 37.5 °C)Bubo has not enlargedHas not received alternative treatment for plagueNo clinical decision to continue anti-plague antibiotics beyond day 10

#### Secondary endpoints

##### Bubonic plague

Proportion of patients without fever (uncorrected axillary temperature < 37.5 °C) at D4Proportion of patients with a pain score < 3 at D4Proportion of patients with a pain score < 3 at D11Mean % change in bubo size at D4Mean % change in bubo size at D11Proportion of patients experiencing a serious adverse event on or before D4Proportion of patients experiencing a serious adverse event on or before D11Proportion of patients experiencing a serious adverse event on or before D21Proportion of patients who are fully adherent to the study treatment schedule

##### Pneumonic plague

Proportion of patients with a therapeutic response at D11. Therapeutic response is defined as follows:
◦ Alive◦ Resolution of fever (uncorrected axillary temperature < 37.5 °C)◦ Resolution of tachypnoea (RR < 24 in adults, but age-specific in children)Proportion of patients without fever (uncorrected axillary temperature < 37.5 °C) at D4Proportion of patients with tachnypnoea resolution (RR < 24 in adults, but age-specific in children) at D4Proportion of patients experiencing a serious adverse event on or before D4Proportion of patients experiencing a serious adverse event on or before D11Proportion of patients experiencing a serious adverse event on or before D21Proportion of patients who fully adhere to the study treatment schedule

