### Objectives {7}

The primary objective of this trial is to test the hypothesis that ciprofloxacin monotherapy given (orally, or for subjects who cannot take oral medications intravenously or in combination) for 10 days is non-inferior to streptomycin (given on days 1–3) followed by ciprofloxacin (given on days 4–10) for the treatment of bubonic plague. The regimens are respectively third- and first-line treatments as per the national plague treatment guidelines in Madagascar.

The secondary objective is to collect data on the effectiveness of ciprofloxacin in the treatment of pneumonic plague, although the trial is not able to formally assess the non-inferiority of ciprofloxacin monotherapy compared to streptomycin and ciprofloxacin combination therapy in pneumonic plague,

Considering the operational and practical complexities of a plague RCT, the study also has additional exploratory objectives to optimize investments: to evaluate the level and kinetics of anti-*Y. pestis* antibodies in bubonic and pneumonic plague during treatment and follow-up, to compare different methods for detection of anti-*Y. pestis* antibodies, to measure the performance of qPCR for plague diagnosis and to allow for the evaluation of new rapid tests that may become available.

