## Assignment of interventions: blinding

### Who will be blinded {17a}

Blinding of patients and the trial team to treatment allocation will not be possible due to the different administration routes of the treatments.

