### Plans to promote participant retention and complete follow-up {18b}

Patients will be provided with a mobile phone upon discharge from the treating centre to optimize retention during follow-up. Community health workers will also assist with reminding patients about their upcoming follow-up visits.

If a patient chooses to withdraw from trial treatment (or the treating clinician believes this is in the best interest of the patient), the patient will continue to receive the standard of care treatment at the discretion of their treating clinician, regardless of the treatment arm to which the patient was randomized. The patient will remain within the trial for the purpose of follow-up, data collection, monitoring and data analysis. Healthcare personnel should explain the importance of allowing existing data to be used, as well as the importance of remaining within the trial for follow-up data collection. If it is not possible to collect further data from the patient at the scheduled trial visits, routine data should be collected via the patients’ medical records.

If a patient withdraws their consent to participate in the trial, data and sample collection will cease and only data up to the point of withdrawal will be used for analysis.

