#### Analysis of secondary endpoints

Descriptive summaries of the data will be provided by randomization arm for the pre-specified secondary outcomes. The data will be summarized by randomization arm using the mean (95% Cl) and median (interval) for continuous or discrete data and raw data with percentages and 95% CIs for binary variables. The average time to resolution of fever and pain at the bubo site will also be summarized.

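### Pneumonic therapeutic response at day 11 omits the two treatment-change criteria used for bubonic plague under the same name, so switched or continued patients can count as responders to their allocated regimen

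*Protocol article*

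**What the plan says.** In the protocol article, Outcomes {12}, Primary endpoint, bubonic therapeutic response has five components. They are listed once for measurable buboes and again for buboes that are palpable but not measurable. Both lists require that the patient has had no alternative plague treatment and that there was no "clinical decision to continue anti-plague antibiotics beyond day 10".

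The pneumonic list under Secondary endpoints uses the same term at the same time point: "Proportion of patients with a therapeutic response at D11. Therapeutic response is defined as follows". Its components are alive, resolution of fever, and "Resolution of tachypnoea (RR < 24 in adults, but age-specific in children"). The list ends there.

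Four other sections decide what this means in practice:

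- Objectives {7}: "The secondary objective is to collect data on the effectiveness of ciprofloxacin in the treatment of pneumonic plague". It adds that non-inferiority in pneumonic plague cannot be formally assessed.
- Plans to promote participant retention {18b}: a patient taken off trial treatment receives standard of care whatever the arm. "The patient will remain within the trial for the purpose of follow-up, data collection, monitoring and data analysis".
- Duration of therapy: "After 10 days, the decision whether to continue therapy will be at the treating" physician's discretion. This is not limited to bubonic patients.
- Who will be blinded {17a}: "Blinding of patients and the trial team to treatment allocation will not be possible".

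**The concern.** A pneumonic patient who does poorly on the allocated drug, is given something else and recovers by day 11 meets all three components. The endpoint then credits the recovery to the allocated regimen.

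The two missing criteria work differently. Alternative treatment is a matter of attribution: the day 11 status may be due to another drug. A decision to continue antibiotics hardly changes status on day 11 itself. It records that the clinician did not regard the course as sufficient, and the bubonic definition treats that as non-response.

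At stake is the main efficacy figure for the secondary objective. No formal test is planned for pneumonic plague, so the response rate by arm with its 95% confidence interval is what readers will take away. The shared label may also lead them to read it as the same quantity as the bubonic rate.

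**Working it through.** **1. Definitions side by side (response at day 11)**

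| Component | Bubonic | Pneumonic |
|---|---|---|
| Alive | yes | yes |
| Fever resolved or absent | yes | yes |
| Local sign | bubo reduced by at least 25%, or not enlarged | tachypnoea resolved |
| No alternative plague treatment | yes | absent |
| No decision to continue antibiotics past day 10 | yes | absent |

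That is five components against three. The local sign has to differ between the two forms; the last two rows do not. The Abstract restates only the bubonic definition, and the missing-data rule in {20c} rests on bubo size, so neither fills the gap.

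**2. Can the situation arise?** Yes. Section {18b} allows a move to standard of care and keeps the patient in the analysis, and Duration of therapy allows continuation. Under Current treatment options, first-line pneumonic treatment is an aminoglycoside combined with ciprofloxacin, which is essentially the control regimen in the pneumonic dosing schedule. A ciprofloxacin-arm patient moved to standard of care would therefore receive roughly the comparator and could still count as a ciprofloxacin responder.

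**3. The plan's own figures.** With n per arm = (1.960 + 1.282)² × 2p(1 − p) / 0.15², then division by 0.90 for 10% loss:

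- Bubonic, p = 0.90: 85 per arm, 95 after loss, 190 in total. The stated figure reproduces.
- Pneumonic, p = 0.75: 176 per arm, 196 after loss, 392 in total.
- Pneumonic, p = 0.80: 150 per arm, 167 after loss, 334 in total.

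The approximately 400 pneumonic patients given under Trial design {8} match p = 0.75, the 25% end of the stated 20–25% case fatality. Since response requires survival, 75–80% is the ceiling on response implied by the protocol.

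**4. Possible overstatement in one arm.** Assumptions, none from the documents: 60% respond without rescue, 10–30% are switched, and 50–75% of those recover.

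Apparent response = 0.60 + (share switched × share recovering)

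- Low: 0.60 + 0.10 × 0.50 = 0.65, an overstatement of 5 points.
- High, uncapped: 0.60 + 0.30 × 0.75 = 0.825, which is above the ceiling.
- High, capped: 0.75 − 0.60 = 15 points, or 0.80 − 0.60 = 20 points.

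The range is about 5 to 15–20 points.

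**5. Effect on the comparison between arms.** Suppose the three-part rate is the same in both arms (0.75 or 0.80), and subtract from each arm the patients who meet it only after alternative or continued treatment (again assumed):

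| Control | Ciprofloxacin | Difference, three-part | Difference, five-part |
|---|---|---|---|
| 5% | 10% | 0 | −5 points |
| 5% | 15% | 0 | −10 points |
| 5% | 20% | 0 | −15 points |
| 10% | 10% | 0 | 0 (both rates fall by 10 points) |

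The omission can hide a difference, or it can shift both rates equally. Which one happens depends on rescue by arm.

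**The case against.** **It may be a deliberate choice.** Status at day 11 regardless of treatment changes is a treatment-policy outcome. That fits an objective worded as effectiveness and the rule that patients who leave treatment stay in the analysis. This stands as a reason to keep the three-part version in the report. It does not explain why the same term means something else for bubonic plague, and the protocol offers no reason.

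**The endpoint is descriptive.** Under Analysis of secondary endpoints, "Descriptive summaries of the data will be provided by randomization arm for the pre-specified secondary outcomes", and pneumonic plague is not powered. This stands, and it limits the severity.

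**Rescue would be partly visible.** Full adherence to the treatment schedule is a separate pneumonic endpoint, and per-protocol populations are planned. Neither changes who counts as a responder. Adherence says nothing about continuation after day 10, and the protocol does not make clear that the per-protocol sets apply to this endpoint.

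**The rule is the same in both arms.** A reader might infer that the bias runs only in favour of ciprofloxacin, since control patients already receive streptomycin. The documents do not support that. Control patients can also leave allocated treatment: the protocol itself cites streptomycin toxicity and stock shortages and names gentamicin as an alternative. Continuation past day 10 is open to both arms, which both take ciprofloxacin to day 10. Open-label decisions, and the fact that standard of care is close to the comparator, make a larger effect in the ciprofloxacin arm plausible, but no rescue rate is given for either arm.

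**Conclusion.** The omission is stated in the text. It is not a detail left to the analysis plan, because the protocol gives a complete pneumonic definition. Patients in either arm who were switched or continued can count as responders to their allocated regimen. The effect is plausibly larger with ciprofloxacin, but its direction and size are not determined by the documents.

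The 5 to 15–20 points rest entirely on the assumed rates, and the upper end also on applying the 20–25% planning case fatality to the ciprofloxacin arm. A reader might take the uncapped 82.5%, about 23 points above the 60% base, as the upper end. It would need a fatality of at most 17.5%, below the protocol's own range.

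A reader might also infer that the trial's main conclusion is at risk. It is not: the primary endpoint already contains both criteria, and the bubonic sample size does not depend on the pneumonic definition. This is a worthwhile correction to a secondary, descriptive and unpowered endpoint.

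**What to change.** 1. Add the two bubonic criteria to the pneumonic definition.
2. Report the current three-part version beside it, labelled as clinical status at day 11 regardless of treatment changes.
3. Tabulate alternative treatment and continuation past day 10 by arm for pneumonic patients.

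If the sponsor prefers to keep the three-part version as the main one, state the reason, give it a name distinct from the bubonic endpoint, and still provide the table. Settle this before pneumonic outcomes are examined by arm; the analysis plan, which {19} says will be written before the trial statistician receives data, is a natural place.

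The cost is endpoint wording and one table. Both items are already needed for the bubonic endpoint; that they are also recorded for pneumonic patients is an assumption to confirm on the case report form. The downside is a lower reported pneumonic response rate. No patient's treatment changes, and no rule on rescue or duration is proposed.

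### For adults with pneumonic plague, tachypnoea at entry is a respiratory rate above 24 but its resolution needs a rate below 24, so a rate of exactly 24 is neither

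*Protocol article*

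**What the plan says.** Two places in the protocol article set an adult respiratory-rate cut-off for pneumonic plague.

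- **Eligibility criteria {10}, Inclusion criteria, Pneumonic plague.** Tachypnoea is an entry criterion, defined for adults as a respiratory rate above 24. The cut-offs for children are described as age-specific, without values.
- **Outcomes {12}, Secondary endpoints, Pneumonic plague.** One component of the D11 therapeutic response is "Resolution of tachypnoea (RR < 24 in adults, but age-specific in children"). The same adult cut-off, below 24, is repeated for the separate endpoint of tachypnoea resolution at D4.

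The same two sections also treat fever. Entry uses a temperature of 37.5 °C or more (or a history of fever), and the response definition uses "Resolution of fever (uncorrected axillary temperature < 37.5 °C").

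On the status of these endpoints, Objectives {7} says that for pneumonic plague "the trial is not able to formally assess the non-inferiority of ciprofloxacin monotherapy" against the combination. Analysis of secondary endpoints adds: "Descriptive summaries of the data will be provided by randomization arm for the pre-specified secondary outcomes".

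**The concern.** A criterion named as resolution of a sign should be met when the sign, as the protocol defines it, is no longer present. For adult tachypnoea that fails at one value. A rate of 24 would not have met the tachypnoea criterion at entry, but at D4 and D11 the same rate is scored as tachypnoea not resolved. On D11 this alone removes the patient from the responders.

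At stake are two of the efficacy endpoints that serve the secondary objective on pneumonic plague: therapeutic response at D11 and tachypnoea resolution at D4. The section on trial design regards the roughly 400 pneumonic cases needed for a formal comparison as unrealistic, so the group is likely to be small and single patients will carry weight in the reported proportions. The trial is also open-label, which is a reason to settle the boundary rule before outcomes are examined.

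**Working it through.** **Inputs, all from the protocol article**

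- Adult tachypnoea at entry: RR > 24 (Inclusion criteria, Pneumonic plague)
- Adult resolution at D4 and D11: RR < 24 (Secondary endpoints, Pneumonic plague)
- Fever at entry: ≥ 37.5 °C; resolution: < 37.5 °C (same two sections)

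**Step 1. Apply both respiratory rules to each whole number near the cut-off.**

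| Adult RR | Tachypnoea by entry rule (> 24) | Resolved by endpoint rule (< 24) | Neither |
|---|---|---|---|
| 22 | no | yes | no |
| 23 | no | yes | no |
| 24 | no | no | **yes** |
| 25 | yes | no | no |
| 26 | yes | no | no |
| 27 | yes | no | no |

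The mismatch is exactly one whole-number value, 24.

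**Step 2. Apply the same check to fever.**

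| Temperature (°C) | Fever (≥ 37.5) | Resolved (< 37.5) | Neither |
|---|---|---|---|
| 37.4 | no | yes | no |
| 37.5 | yes | no | no |
| 37.6 | yes | no | no |

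The fever rules are exact complements. Of these two pairs, only the respiratory one has a gap.

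**Step 3. Close the gap.** Pairing > 24 with ≤ 24, or ≥ 24 with < 24, leaves no value in the last column. Either repair works arithmetically.

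**Step 4. Size.** Let *a* be the adult share of pneumonic patients, *r* the share of adults who meet the D11 response if a rate of 24 counts as resolved, and *s* the share of those recorded at exactly 24. The reported overall proportion is then lower by

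fall = *a* × *r* × *s*.

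The article gives none of the three, so the fall cannot be computed. For illustration only, assume *a* = 0.60, *r* = 0.75 and *s* between 0.05 and 0.10:

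- 0.60 × 0.75 × 0.05 = 0.0225, or about 2 percentage points
- 0.60 × 0.75 × 0.10 = 0.045, or 4.5 percentage points

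**Step 5. Confirm that the main design is untouched.** Sample size {14} uses only the bubonic endpoint: 90% response in both arms, margin 15%, one-sided 2.5%, power 90%, 10% loss.

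- Per arm: (1.960 + 1.282)² × (0.90 × 0.10 + 0.90 × 0.10) / 0.15² = 10.51 × 0.18 / 0.0225 = 84.1, rounded up to 85
- With 10% loss: 85 / 0.90 = 94.4, rounded up to 95
- Both arms: 2 × 95 = 190, as stated

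No respiratory rate enters this calculation or the bubonic primary endpoint.

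**The case against.** The best defence is that entry and recovery criteria do different jobs and need not be complements. Asking for a rate strictly below the threshold before calling tachypnoea resolved is a tenable, slightly conservative rule. It is also complete: at follow-up every adult rate is either below 24 or not, so nobody is unclassifiable. The same rule applies in both arms, and the endpoints are descriptive.

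Part of this stands. A stricter recovery rule is possible, and it is too strong to call adults at 24 misclassified, since they are classed as the endpoint section directs. However, the article nowhere says that a stricter target is meant. It names the criterion as resolution of the entry sign, and it handles fever with exactly complementary limits. The difference should be either removed or declared.

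A reader might infer several stronger things that the article does not support:

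- **A fall of 5 to 10 percentage points in reported response.** This would need 5 to 10% of recovering adults to sit at exactly 24, a share the article does not give. It would also need every pneumonic patient to be an otherwise-responding adult. Children and patients who die or remain febrile dilute the effect.
- **That 24 is an especially common recorded value** because rates are counted over 15 or 30 seconds and multiplied up. The article does not state a counting method.
- **A matching error for children.** Their cut-offs are not printed in this condensed article, so no mismatch can be shown.
- **That the endpoint symbol is the wrong one.** The article does not show which of the two was intended.

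**Conclusion.** The inconsistency is real and small. Read as written, an adult at exactly 24 has no tachypnoea by the entry definition but is counted as unresolved at D4 and D11 and, on D11, as having no therapeutic response even if alive and afebrile. It follows directly from the two stated cut-offs and rests on no assumption beyond rates being recorded as whole numbers.

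Its reach is limited to one value, to adults, and to descriptive secondary endpoints in a group for which no formal non-inferiority assessment is intended. The direction is known: the adult response and resolution proportions can only be lowered relative to the complementary rule. The amount is not known, and the 2 to 4.5 points above are purely illustrative. Nothing suggests a difference between arms, and the bubonic non-inferiority conclusion is not affected. This is a clarification worth making, not a threat to the trial.

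**What to change.** Reconcile the pneumonic inclusion criteria with the pneumonic secondary endpoints so that adult resolution is the exact complement of the tachypnoea definition used at entry. Because the trial is ongoing, the simplest place is the endpoint definition, at both D4 and D11: the patient no longer meets the entry definition of tachypnoea. This leaves eligibility unchanged and does not require a judgement here on which number is clinically preferable.

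If a stricter recovery threshold is intended, state that it is deliberate and also tabulate both endpoints with the complementary cut-off.

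Either way, settle the rule before outcome data are examined by arm. The cost is a minor endpoint amendment, which under the protocol's amendment procedure {25} goes to the Trial Operations Committee and the ethics committees. No new data are needed, since vital signs are already scheduled on D4 and D11 (Table 1).
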